### Randomization and intervention

#### Allocation and blinding

Participants will be randomized to 1 of 3 groups:

placebo,600 mg/day gabapentin, or1,800 mg/day gabapentin.

Group assignment will be stratified within each group based on AIS grade. A randomized stratified block design will be used with 3 blocks of size 7 within each cohort (AIS A–B and AIS C–D). A statistician will create a list under this design prior to enrollment of the first participant.

Blinded assessors will be designated for this study. The remainder of the study team will not be blinded to monitor all aspects of the trial. Blinding will be maintained by using the blinding plan described here to follow throughout the study.

The blinded assessors will be independent from the medical team and the research staff.Interactions between the blinded assessors and participants will be limited.Blinded assessments will be performed in a private room.The blinded assessors will be reminded prior to each assessment of the importance of blinding and to not engaging in extra “chit chat” with participants (and family/caregivers) or other study staff.Participants (and family/caregivers) will be informed of the importance of blinding overall at the beginning of the study and will be reminded prior to each blinded assessment to make sure he/she does not tell the blinded assessor(s) which group they are in.Blinded assessors will not review any previous blinded assessments.Blinded assessors will review the ‘Study Blinding Checklist' immediately before each blinded exam and will complete the ‘Blinding Verification Questionnaire' immediately after each blinded exam.If a participant becomes unblinded to his/her treatment group, every effort will be made to keep the blinded assessors blinded.If a participant develops neuropathic pain during the 90-day treatment window and the clinical team decides all other neuropathic pain treatments are ineffective, impractical, or contraindicated, study drug will be stopped and standard of care gabapentinoids may be used. The participant will not be withdrawn from the study, though, unless he/she desires to be withdrawn. Study drug will no longer be given, but any remain study visits will be completed. The blinded assessors will remain blinded of all knowledge that the study drug has been stopped.

Attempts will be made to blind participants, but as described below, the placebo and gabapentin capsules will not be identical.

#### Intervention

Study medication will be started within 120 h post-injury and continued for 90 days. Both treatment groups (600 or 1,800 mg/day gabapentin) will receive 2 capsules of gabapentin by mouth 3 times per day for 90 days. Gabapentin dose will be gradually increased upon initial administration to reach the target dose and will be gradually decreased at termination (26). During acute hospitalization, gabapentin will be provided by the inpatient research pharmacy. At discharge, the study clinician will order the remaining supply from the research pharmacy and tapering instructions will be clearly provided to the participant. Participants temporarily unable to swallow pills by mouth (i.e., those required feeding tubes) will receive gabapentin dissolved in water at the same dosage.

The control group will receive 2 placebo capsules consisting of inert cellulose by mouth 3 times per day for 90 days. Placebo doses will be tapered up and down in the same manner as gabapentin. The capsules will be prepared by a compound pharmacy (Klein's Pharmacy, Cuyahoga Falls, Ohio) and will be administered by the research pharmacy. Participants unable to swallow pills by mouth will receive placebo dissolved in water.

All participants will be asked to abstain from taking additional gabapentinoids, (such as pregabalin or additional doses of gabapentin), during the 90-day treatment period. Person-specific treatment plans for neuropathic pain affecting function or quality of life will be deferred to the clinical team. No other clinical treatments will be restricted. Evidence-based alternative treatments include (but are not limited to) amitriptyline, tramadol, lamotrigine, transcutaneous electrical nerve stimulation (TENS), and oxycodone (27). If the clinical team decides all other pain treatments are ineffective, impractical, or contraindicated, the study drug will be stopped and standard of care gabapentinoids may be used.

### Assessments

After consent, randomization, and the initiation of treatment (all occurring no later than 120 h post-injury), follow-up will occur based on the schedule of visits listed in Table 2. To mimic potential timing of visits in a future efficacy trial, we included a Baseline, End of Treatment, and End of Study visit, which include the exploratory blinded efficacy and unblinded safety assessments. The timing of the Baseline visit (7 days post-injury ±2 days), which is just after start of study medication, is related to the complexity of performing outcome assessments in the immediate few days after injury. This approach has been used in several acute intervention trials in SCI (28–32). The Interim visit is included primarily to monitor pain transitions. The total length of each participant's time in the trial is 6 months.

**Table 2 T2:** Schedule of visits.

	**Screening**	**Baseline (7 dpi+/−2d)**	**Interim (30 dpi+/−5d)**	**End of 90 day treatment(+14 d)**	**End of study (180 dpi +/−14d)**
**Consent**					
Informed consent form	X				
**Eligibility**					
Inclusion/Exclusion criteria	X				
**Exploratory blinded efficacy assessments**					
ISNCSCI		X	X	X	X
ISAFSCI		X		X	X
SCI-SET		X		X	X
SCIM III		X		X	X
ISCI QoL BDS		X		X	X
**Exploratory unblinded safety assessments**					
DN4		X	X	X	X
ISCI Pain BDS v2		X	X	X	X
Study medication log		X	X	X	
Adverse events		X	X	X	X
Concomitant medication log		X	X	X	X
Exit form					X

DPI, days post-injury; ISNCSCI, International Standards for Neurological Classification of SCI; ISAFSCI, International Standards for Autonomic Function after SCI; SCI-SET, SCI Spasticity Evaluation Tool; SCIM III, Spinal Cord Independence Measure version 3; ISCI QoL BDS, International SCI Quality of Life Basic Data Set; DN4, Douleur Neuropathique 4 Questionnaire; ISCI Pain BDS v2, International SCI Pain Basic Data Set version 2.

#### Primary feasibility assessments

The primary endpoint of this trial is feasibility. Table 3 lists the measures and quantitative benchmarks of success for the following four feasibility questions:

Can the target population be recruited?Can the drug treatment protocol be delivered?Can the assessors remain blinded?Will participants complete the study?

**Table 3 T3:** Analytical questions, measures, and benchmarks of success.

**Question**	**Measure**	**Quantitative benchmark of success**
Can the target population be recruited?	Number screened/month; number enrolled/month; reasons for not enrolling	Screen an average of 4/month; Enroll an average of 1/month
Can the drug treatment protocol be delivered?	Proportion of enrolled who receive the full drug treatment protocol (placebo arm; two gabapentin dose arms); number of dosing deviations/arm; reasons for dosing deviations	70% enrolled in placebo arm receive full dosing protocol; 70% enrolled in each gabapentin arm receive full dosing protocol
Can the assessors remain blinded?	Number of occurrences of unblinding; reasons for unblinding	5% or fewer occurrences of unblinding
Will participants complete the study?	Retention rate; reasons for dropout; proportion of planned assessments completed	70% of participants stay enrolled until the end of the study and complete 3 of the 4 assessment visits

#### Exploratory efficacy assessments

The International Standards for Neurological Classification of SCI (ISNCSCI) was selected as the most important blinded assessment of neurologic change (33) because of the emerging evidence suggesting that early gabapentin has a positive effect on motor-based neurologic recovery. An unblinded clinical assessment of neurologic level of injury will be used during screening to verify eligibility, but a blinded full ISNCSCI exam will be performed at all other visits. The ISNCSCI will provide multiple neurologic outcomes, including upper extremity motor score, lower extremity motor score, total motor score, light touch sensory score, pinprick sensory score, deep anal pressure, voluntary anal contraction, zone of partial preservation, and AIS grade data.

The International Standards for the documentation of Autonomic Function after SCI (ISAFSCI; (34, 35) was recently revised by the Autonomic Standards committee of the American Spinal Injury Association (36). As the revised ISAFSCI has not yet been validated and because emerging human data evaluating the effect of early gabapentin on autonomic function are not yet available, we chose to evaluate autonomic function in an exploratory manner. The cardiovascular, bladder, and bowel components of the revised ISAFSCI will be used. The cardiovascular component measures heart rate and blood pressure changes before and after a sit-up tilt test. Categorical scores are also assigned based on standardized definitions of autonomic responses. The bladder component measures sensation in the T11-12 and S3-5 dermatomes and motor function in the S3-5 dermatomes, which are then assigned a categorical score related to awareness of bladder fullness and ability to prevent bladder leakage. The bowel component measures the sensory and motor preservation at the S3-5 dermatomes, then assigns categorical and subjective scores related to awareness of bowel fullness and ability to prevent bowel leakage.

If early administration of gabapentin reduces maladaptive plasticity, as suggested by preclinical evidence, it may also be important to measure spasticity in a future efficacy trial (12, 13). Additionally, gabapentin has been used previously for the management of spasticity (37, 38). Spasticity is multi-faceted and can have both positive and negatives impacts on the individual. The validated Modified SCI Spasticity Evaluation Tool (SCI-SET) will be used (39). This is a self-report tool and data will be obtained through interview. The Modified SCI-SET contains 33 items that measure the positive or negative effects of spasticity on activity and participation, using a 4-level rating scale.

It will also be important in the future to link neurologic changes with functional changes. There is a known relationship between ISNCSCI motor scores and the Spinal Cord Independence Measure version 3 [SCIM III; (18, 40)]. Therefore, the SCIM III will be used as an exploratory measure of global function (41, 42). The SCIM III measures self-care, sphincter and respiration, and mobility; a score is assigned for each category of function, which is summed to generate a final score between 0 and100. SCIM III data will be obtained through interview.

Ultimately, any neurologic and functional improvement should have an impact on quality of life. For this exploratory measure, the validated International SCI Quality of Life Basic Data Set [ISCI QoL BDS; (43, 44)] was chosen. The ISCI QoL BDS is a 3-item subjective measure of an individuals' personal perspective of his/her quality of life as a whole, satisfaction with physical health, and satisfaction with psychological health. A score between 0 and 10 is assigned to each question. The ISCI QoL BDS data will be obtained through interview.

#### Unblinded safety assessments

##### Pain

As gabapentin is a first-line treatment for SCI-induced neuropathic pain and participants will be randomized to a low- or medium-dose gabapentin or placebo for the first 3 months' post-injury, it is important to track pain and its potential interference throughout the study period. The International SCI Pain Basic Data Set (ISCI Pain BDS) version 2 will be used for this as it has been well validated (45–47). Though most below-level neuropathic pains develop progressively between 1- and 12-months' post-injury, pain can develop immediately in a small subset of individuals (48). It may be necessary to exclude individuals that develop hyperacute below-level neuropathic pain from a future efficacy trial. It can be challenging to identify below-level neuropathic pain in the acute trauma setting and differentiate it from other acute pains. Therefore, in addition to the ISCI Pain BDS, we will use the Douleur Neuropathique 4 (DN4) on up to 2 below-level pain locations. The DN4 will objectively separate neuropathic pain from other pains (49, 50). The ISNCSCI data in combination with the ISCI Pain BDS can objectively determine above, at-, or below-level classification. The ISCI Pain BDS can objectively rate the pain intensity and interference. This should enable the ability to track the transition from acute to chronic pain during the 6-month study period.

##### Adverse events

It is very common for individuals that sustain a traumatic SCI to experience complications, most commonly within the first 14 days' post-injury. The most frequent types of moderate-severe complications are respiratory failure, pneumonia, pleural effusion, anemia, cardiac dysrhythmia, and severe bradycardia (51). We will track general complication adverse events (AEs) based on the following organ/systems: pulmonary, infectious, hematologic, cardiac, gastrointestinal/genitourinary, skin, and neuropsychiatric. We will also track AEs based on the known risk profile of gabapentin in SCI (dizziness, nausea, somnolence, peripheral edema, weakness/fatigue, diarrhea, constipation, blurred vision, headache, dry mouth, itching). All AEs will be evaluated for severity, expectedness, and relatedness following FDA and IRB guidelines.

A designated Medical Monitor (MM) will monitor for clinical safety. The MM will be a MetroHealth traumatologist who has extensive experience managing severely ill surgical and trauma patients in the intensive care setting and, thus, is well suited to monitor this acute intervention. AE reports will be provided to the MM on a quarterly basis. The MM will examine all AEs for reportability (unexpected, related or possibly related, AND resulting in increased risk). Non-reportable AEs will be documented internally and included in IRB continuing reviews. The study team will also have access to the MM in real time to address any urgent safety issues that may arise. A safety report will be generated annually to coincide with IRB continuing review.

Discontinuation criteria are as follows:

If a participant's medical condition deteriorates due to disease progression, the PI in consultation with the clinical team may withdraw the participant.If a participant develops neuropathic pain during the 90-day treatment window and the clinical team decides all other neuropathic pain treatments are ineffective, impractical, or contraindicated, study drug will be stopped and standard of care gabapentinoids may be used. The participant will not be withdrawn from the study, though, unless he/she desires to be withdrawn. Study drug will no longer be given, but any remain study visits will be completed.

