#### Sample size

Studies analyzing feasibility are not intended to determine statistical significance, therefore traditional sample size calculations to power efficacy are inappropriate (21, 22). Rather, sample size should be large enough to yield useful data to answer the feasibility questions. There are several rules of thumb for determining a sample size for a feasibility study (typical range is 12–35 participants per arm; (23, 24). As described below, our most important neurologic outcome measure will be the ISNCSCI (all existing human data demonstrating effect of gabapentin on neurorecovery has been derived from the ISNCSCI). Differences in natural recovery due to injury severity could influence variability in ISNCSCI scores, with individuals that are AIS A or B being more similar than those that are AIS C or D (25). Therefore, we chose to stratify randomization into the 3 arms based on AIS grade (see Table 1). We will enroll 14 participants into each arm (with equal stratification of A–B and C–D in each arm). Therefore, our target sample size to complete the entire study will be 42.

**Table 1 T1:** Sample size and randomization cohorts.

**Arm**	**AIS A–B**	**AIS C–D**
Treatment 600 mg/day	7	7
Treatment 1,800 mg/day	7	7
Placebo	7	7

AIS, American spinal injury association impairment scale.

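### The rule for deterioration due to disease progression lets an unblinded PI end a participant's follow-up, while the adjacent pain rule stops study drug and keeps the visits

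*Protocol article*

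**What the plan says.** The Adverse events section of the Protocol article lists two discontinuation criteria.

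- **Deterioration:** if the medical condition worsens through disease progression, "the PI in consultation with the clinical team may withdraw the participant". There is no threshold and no statement on whether outcome visits continue.
- **Neuropathic pain that other treatments cannot manage:** study drug stops, but "The participant will not be withdrawn from the study, though, unless he/she desires to be withdrawn". The text adds: "Study drug will no longer be given, but any remain study visits will be completed".

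On who knows the arm, Allocation and blinding designates blinded assessors and then says: "The remainder of the study team will not be blinded to monitor all aspects of the trial". The PI is not named, but falls within that remainder.

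Table 3 (Primary feasibility assessments) sets the retention benchmark: "70% of participants stay enrolled until the end of the study and complete 3 of the 4 assessment visits". The measures behind it are: "Retention rate; reasons for dropout; proportion of planned assessments completed". Primary data analysis makes the feasibility conclusion depend on meeting all the benchmarks. Secondary data analysis uses the feasibility SD, through the upper limit of its 80% confidence interval, and the blinded total motor score to inform the sample size of a later trial. It also uses the retention rate to estimate that trial's duration.

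**The concern.** Stopping a drug and leaving a study are separate events, and the pain criterion keeps them apart. The deterioration criterion does not. Because the neighbouring rule says explicitly that its participants are not withdrawn from the study, the natural reading of the first rule is that its participants are.

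The choice is discretionary, it is made by someone who knows the allocation, and its trigger may be related to the neurological outcome being tracked. Loss of that kind is not random. Two uses of the data are exposed:

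1. **Retention.** Table 3 asks whether participants will complete the study. An investigator's decision to withdraw someone is scored in the same way as a participant's decision to leave.
2. **Motor score.** If those withdrawn tend to have low scores, the observed mean rises and the observed SD falls, and the SD is carried into planning the efficacy trial.

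**Working it through.** **Inputs from the article.** Sample size: "We will enroll 14 participants into each arm (with equal stratification of A–B and C–D in each arm". With three arms and 7 per AIS stratum, 3 × 2 × 7 = 42, which reproduces the stated total. The retention benchmark is 70%.

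**Inputs that are assumptions, because the article gives none.** r is retention apart from PI withdrawals, w is the proportion withdrawn by the PI, and the shape of the motor-score distribution and its link with deterioration are also assumed.

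**Step 1: direction of the effect on retention.** 0.70 × 42 = 29.4, so 30 must be retained and at most 12 may be lost. A withdrawn participant has not stayed enrolled and fails the benchmark, even with three visits already done. With k PI withdrawals, 12 − k other losses are allowed: 10, 8 and 6 for k = 2, 4 and 6. The rule therefore makes the benchmark harder to meet. It would become easier only if withdrawn participants left the denominator. For k = 4, 0.70 × 38 = 26.6, so 27 would be needed and 11 other losses allowed instead of 8. The article does not say that this is done.

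**Step 2: size of the effect on retention.** The chance of passing is P(X ≥ 30) with X ~ Binomial(42, r(1 − w)).

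| r | w = 0 | w = 5% | w = 10% | w = 15% |
|---|---|---|---|---|
| 0.75 | 77% | 57% | 36% | 19% |
| 0.80 | 94% | 81% | 61% | 39% |
| 0.85 | 99% | 95% | 83% | 62% |

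**Step 3: size of the effect on the motor-score SD.** The largest effect arises if exactly the lowest fraction p of a normal distribution is lost. With a = Φ⁻¹(p) and λ = φ(a)/(1 − p), the remaining variance is 1 + aλ − λ². For p = 0.10, a = −1.282 and λ = 0.1755/0.90 = 0.195, so the variance is 1 − 0.250 − 0.038 = 0.712 and the SD factor is 0.84. Required sample size scales with the variance.

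| Assumed pattern of loss | Loss | SD factor | Sample-size factor |
|---|---|---|---|
| Exactly the lowest scores, normal | 5% | 0.90 | 0.81 |
| Exactly the lowest scores, normal | 10% | 0.84 | 0.71 |
| Exactly the lowest scores, normal | 20% | 0.76 | 0.58 |
| Graded: loss more likely at lower scores | 10% | 0.94 to 0.98 | 0.89 to 0.97 |
| Lowest scores, two-cluster mix of severities | 10% | 0.95 to 0.99 | 0.89 to 0.98 |
| Unrelated to motor score | 10% | 1.00 | 1.00 |

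At 10% loss the SD therefore shrinks by between nil and about 16%.

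**Step 4: comparison with the planned safety margin.** The upper 80% confidence limit raises the SD by a factor of 1.11 to 1.18 when pooled over arms (39 degrees of freedom) and 1.23 to 1.36 for one arm of 14; the lower figure is the one-sided limit and the higher the two-sided. At 10% loss the pooled margin is larger than the shrinkage in every pattern except strict truncation, where 0.84 × 1.11 = 0.93 and 0.84 × 1.18 = 0.99. That margin is meant for sampling error, however, and does not correct a bias.

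**The case against.** Several arguments against the point have force.

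- **The rule is narrow.** A reader might infer that anyone who deteriorates can be removed at will. The text requires deterioration due to disease progression and consultation with the clinical team. This stands, although no blinded person is part of the decision.
- **Frequent use is not shown.** The same section says that complications are common in the first 14 days, and a reader might infer that the rule will often be triggered. The article lists those complications as adverse events to track. It does not call them disease progression, and pneumonia or anemia need not mean a low motor score. This stands: neither the rate nor the link is known.
- **Retention is not flattered.** A reader might infer that removing poor courses improves the benchmark. Step 1 shows the opposite. Reasons for dropout are also recorded, which supplies much of the information needed to tell the two kinds of loss apart. What remains is that the benchmark figure itself does not separate them.
- **A large planning error is not established.** If exactly the two lowest of 14 in an arm were lost, the SD factor would be 0.83, and a sample size built on the raw SD would be about 32% too small (0.83² is about 0.68). Nothing supports that pattern, and the plan refers to the upper confidence limit. With a correlation of 0.5 between deterioration and score, the factor is 0.96 and the shortfall about 8% (0.96² is about 0.92). Motor results are exploratory and no efficacy test is planned.
- **Differential use by arm is only possible.** Nothing suggests it. Equal use would leave contrasts between arms largely unaffected.
- **The article is condensed.** The deterioration sentence does not contain the word study, and the full protocol may say more. But the article does fix the two rules side by side with different follow-up. If only study drug was meant, the sentence needs correcting anyway.

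**Conclusion.** The point holds in a limited form. As written, one criterion keeps follow-up and the other lets an unblinded PI, after consulting the clinical team, end it. The resulting loss may be related to outcome and is decided with the arm known.

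For the primary endpoint, the effect is a benchmark that is harder to meet and harder to interpret. If 80% would otherwise be retained, PI withdrawal of 5% or 10% lowers the chance of passing from 94% to 81% or 61%. For planning, the SD could be too small by nil to about 16% at 10% loss. Both ranges rest on assumed rates and an assumed link with motor score. They show that bias is possible, not that it will occur. This is an inexpensive improvement worth making, and it does not undermine the design.

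**What to change.** Reconcile the two discontinuation criteria on follow-up:

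1. In the deterioration criterion, state separately what happens to study drug and what happens to study participation. The clinical decision on study drug stays as it is. For participation, say that remaining visits are completed as far as feasible for participants who remain willing, as the pain criterion already provides.
2. In the retention row of Table 3, report investigator-initiated withdrawals separately from participant-initiated dropout, and state that both stay in the denominator.

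The cost is about one sentence in the criterion and one line in the table. In use, some visits in very ill participants will be partial or missed. The wording must also respect withdrawn consent and loss of capacity, since the trial deliberately enrolls only people able to consent for themselves.
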